#### Plans to promote participant retention and complete follow-up

General practices are study sites and are responsible to provide continuous telephone-monitoring. The following data will be collected from all study participants: ID, gender, date of the informed consent, treatment ended (yes/no), date of end of treatment as well as reasons, request to delete data (yes/no), date and time of the dataset created; as well as data on their individual assessments and monitoring, when available. The following data will be collected from all study sites/general practices: ID, practice identification number (Betriebsstättennummer, BSNR), date and time of the dataset created.

#### Data management, Confidentiality

The evaluating institution (Department of General Practice and Health Services Research, University Hospital of Heidelberg) receives pseudonymized data only and cannot assign data to individuals.

Data collected in the CovidCare-module are secured in the general practices.

Pseudonymized data from patients who have given their informed consent is transferred to the study central office weekly. Data include all pseudonymized data collected in the initial assessment and the telephone monitoring as described in the intervention description.

Patients in each general practice are given a sequential number, which is linked to the corresponding general practice in the data. For the purpose of the identification of general practices, they export their unique license key as well as their practice identification number. In the study central office, a list linking the license key and the BSNR to a practice name and address data is stored separately and secured.

Data will be transferred via a secure unidirectional way (Zentraler Daten-Austausch-Container/ Kryptographie- und Transfer-Modul, ZeDaC-KTM). The ZeDaC-KTM interface allows for flexible, universal, and secure data exchange between health care organisations and their partners (here: Dept. of General Practice and Health Services Research). Hybrid encryption is used, which combines the benefits of asymmetric (public-key cryptosystem RSA (4096 bit)) and symmetric encryption (Advanced Encryption Standard (AES) 256 bit). The key length lies above the recommendations of the Federal Office for Information Security. This means that data that is temporarily stored on the ZeDaC-KTM server for the purpose of data transfer is encrypted and not readable. Only when data is collected from the server by the study central office, the encryption is reversed.

Digital data from questionnaires, interviews, and the CovidCare software module is stored on database-servers at the Department of General Practice and Health Services Research, University Hospital Heidelberg and are only accessible by the study team. Servers are in a separate room that can only be accessed by authorized personnel of the IT-team. Servers are not connected to the internet and cannot be accessed externally. All system users must have personalized access to the network of the University Hospital Heidelberg. Additionally, users must have a personalized user account in order to access the server. Data on the server is secured on the data storage of the data center of the University Hospital Heidelberg on a daily basis.

Data is secured for 10 years after the completion of the study or until a participant withdraws his/her consent to participate and demands to have data already collected destroyed, and will then be destroyed irretrievably.

Anonymized data only will be used for publications.

The existing data protection concept of the CareCockpit, proven by all partners will be used.

The principle investigator is responsible for data processing.

#### Plans for collection, laboratory evaluation and storage of biological specimens for genetic or molecular analysis in this trial/future use

Not applicable, as this is not an ancillary study.

### Statistical methods

#### Statistical methods for primary and secondary outcomes

Data analysis is explorative. Date of the full study population (general practices and patients) will be included in data analysis.

Descriptive statistics of all collected data will be performed. Continuous variables will be described using means, standard deviations, median, minimum, maximum, and first and third quartile. Categorical variables will be reported using absolute and relative frequencies.

The potential effect of sociodemographic characteristics (age, gender, living situation), risk factors (as described above) on the severity of the disease, utilisation of different care services (hospitalisation, intensive care unit, invasive ventilation, palliative care) will be estimated by models taking the clustered structure into account. Therefore, e.g. SAS PROC MIXED, PROC GENMOD or PROC GLIMMIX can be accordingly parametrized to determine fixed and random effects. In order to determine potential differences concerning mortality between particular strata there are also a couple of methods available to take a clustered structure into account. One option is a likelihood-based random effects (frailty) model. The baseline hazard could be either a priori determined (e.g., Weibull) or approximated by piecewise constant counterpart. The estimation could be carried out by adaptive Gaussian quadrature method which is implemented in SAS PROC NLMIXED.

Incubation, begin of the disease, and progression of the disease will be analysed descriptively.

Data analysis for the process evaluation is descriptive and explorative. Qualitative data from interviews will be transcribed according to established standards and will be analyzed with regard to the research questions with qualitative content analysis [17] or framework analysis using the software MAXQDA. Quantitative survey data and the indicators for the intervention fidelity will be analyzed descriptively.

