### Eligibility criteria {10} and informed consent

All GPs who participate in general-practice centred care (GP-centred care) by the AOK Baden-Württemberg care are eligible for using the CovidCare-module within the CareCockpit software. The eligible practices are informed by the GP-centred care contract partners about the possibility to use CovidCare for the care of confirmed and suspected COVID-19 patients.

Prerequisites are the online registration and participation in an online training including exam questions for the handling of the software. After the successful completion of the exam, general practices can download the software.

All general practices who have successfully completed the exam and who download the software are automatically provided with an invitation for participation in the CovidCare study as well as an information leaflet and a participation form.

General practices can participate in the CovidCare study by sending the signed participation form to the study central office (Department of General Practice and Health Services Research, University Hospital Heidelberg).

Additional time expenditure for GP-practices for participation in the study concern information of eligible patients, obtaining the informed consent as well as the weekly data transfer. Time expenditure for this study depends on the number of patients a general practice can include in the study.

The study population comprises of COVID-19 patients treated in general practices who meet the inclusion criteria. The study population for the process evaluation consists of GPs, VERAHs (Care Assistant in General Practice (*Ver*sorgungs*a*ssistentin in der *H*ausarztpraxis)) and patients participating in the CovidCare study.

The following groups of patients are eligible for participating in the study:

COVID-19 patients aged 18 or older (as per definition patients with symptoms of an infection of any severity and positive test for SARS-CoV-2), who are in domestic isolation* and who have at least one risk factor**

OR

2.Patients aged 50 and older with a clinically urgent suspicion of COVID-19 (such as acute respiratory symptoms of any severity), without verification of SARS-CoV-2 and who have at least one risk factor**/***

*Domestic isolation: includes persons for whom the authorities highly recommend further social distancing beyond the restrictions as currently ordered.

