### Intervention description

Measures within the CovidCare-module include patient intake, an initial assessment and several telephone monitoring calls. In the initial assessment, information on risks (age, obesity, nicotine consumption, diabetes, cardiovascular disease, pulmonary disease, chronical hepatic disease, chronical nephrological disease, immunodeficiency, treatment of oncological disease with immunodeficiency, vaccination status), gender, SARS-CoV-2 status, living condition and SARS-CoV-2 status of contact persons, symptom history, legal information (health authorisation, patient decree) is collected and inclusion in the telephone monitoring is defined. The GP individually sets the presumable date of onset of COVID-19 and the extent and frequency of the telephone monitoring. GP-ascertained begin of COVID-19 equals to day 1. GPs are responsible to consider the appropriate monitoring intervals referring to the actual clinical knowledge base regarding the disease course with milestones for deterioration and recovery.

Patients are provided with a monitoring protocol that can be individualized, e.g. for daily log of symptoms and vital signs. The telephone monitoring includes a monitoring of symptoms and signs of infection and the cardio-respiratory system. Individual timelines and figures are created and provide an overview on first symptoms (presumable disease onset), positive test result, disease progression. This aids in assessing the state of health and early detection of a deterioration. A total number of at least three to four contacts is recommended, including the intake, the initial assessment and a closing contact. Any further contacts should be conducted in the critical phase as defined by the knowledge base provided by the RKI [12, 13], the frequency is to be increased with a deterioration. The closing contact includes a short closing documentation not later than three weeks after disease onset. In this closing contact, information on the utilisation of different health care services (e.g. hospitalisation, ventilation) are retrieved and documented.

No further telephone monitorings are conducted when (a) the patient is cured (defined as alive and without symptoms of COVID-19 for 48 h and longer), (b) the patient is hospitalised, (c) the patient has passed away, (d) none of the above has happened not later than three weeks after first symptoms showed.

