### Outcomes

The primary outcome is hospitalisation due to COVID-19. The following indicators have been identified as secondary outcomes:

Diagnosis of pneumonia in confirmed and suspected COVID-19 patients [14].Utilisation of palliative care by confirmed and suspected COVID-19 patients during quarantine or stay at hospital.Mortality rate of confirmed and suspected COVID-19 patients (death at home, death in hospital, death in long-term care institution).Anxiety in confirmed and suspected COVID-19 patients using the Generalized Anxiety Disorder Index (GAD-2) [15].Identification of predictive risk factors for the outcomes such as hospitalisation, intensive care and mortality.

For the process evaluation we chose an exploratory sequential design. The process evaluation consists of a qualitative strand and a quantitative strand.

Overall, for the process evaluation we use the RE-AIM framework according to Glasgow and colleagues [16] to assess reach, efficacy, adoption, implementation and maintenance of the CovidCare surveillance and care tool. Table 1 provides an overview of the outcomes, indicators and methods/instruments of the process evaluation according to the RE-AIM framework.

**Table 1 Tab1:** Concept of the process evaluation

Outcomes	Indicators (examples)	Methods/Instruments
1) Reach The extent to which patients are reached by the implementation of CovidCare as well as the number of patients who are willing or refused to participate in CovidCare.	• How have patients been approached • Number of patients approached • Number of patients willing to participate in CovidCare • Patients: Reasons for refusal and drop-out, exclusion rate • Number of contacts per patient (i.e. telephone monitoring, particularly in the critical phase as defined by the RKI as a proxy whether GPs treat their patients according to guidelines) • Characteristics of participating patients	S, I, DB
2) Efficacy The efficacy of the CovidCare-module includes positive and negative impacts/effects for patients and HCP as well as the patients’ quality of life and the patients and the HCP’s satisfaction with the intervention.	• Positive and negative effects on patients’ quality of life, perception of (quality of) care, disease coping • Effects on health care personnel in managing Covid-19 patients • Satisfaction of HCP and patients with CovidCare • Comparison with patients with Covid-19/suspected cases but WITHOUT additional risk factors or aged >50	S, I, DB

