### Data collection and management

#### Plans for assessment and collection of outcomes

Data sources for the evaluation are data collected within the CovidCare-module within the CareCockpit software in general practices in Baden-Wurttemberg. The CareCockpit software, developed and licensed by the Department of General Practice and Health Services Research at the University Hospital Heidelberg, is designed for case management in general practices and is currently used in approx. 700 general practices in Baden-Wurttemberg. The CovidCare-module therefore is an extension of the electronic patient record in general practices and supports GPs to take care of confirmed and suspected COVID-19 patients in a structured and standardized way. The CovidCare-module has been recently developed and is implemented in general practices within GP-centred by the AOK Baden-Württemberg.

The following data will be recorded from general practices: ID, practice identification number, date and time of the dataset created.

In an initial assessment and telephone monitoring, potential risk (risks) factors are recorded and symptom progression is documented.

Consequently, the following data will be recorded from patients:

ID, gender, date of the informed consent, treatment ended (yes/no), date of end of treatment as well as reasons, request to delete data (yes/no), date and time of the dataset created; data on their individual assessments (examples: ID, date of assessment, ID of VERAH who conducts the assessment, age, diabetes, cardiovascular data, data on pulmonary diseases, liver diseases, immune system, medication, cancer diseases, other diseases, hospitalisation, obesity, smoking, pneumococci, influenza, medication regimen) and monitoring, when available (examples: ID, date and time and place of the dataset created, ID of VERAH who conducts the monitoring, anxiety, medication, patients’ condition as well as symptoms and course of the disease, cured, deceased).

Data sources for the process evaluation are questionnaires and qualitative telephone interviews with GPs, VERAHs and patients using self-developed semi-structured interview guides (see Additional files 1 and 2) and paper-based questionnaires according to the RE-AIM framework (see Table 1) as well as data from the CovidCare-module. Self-developed questionnaires will be presented to the ethics committee in an amendment.

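### Entry rules let time at risk differ by age, but the hospitalisation models include neither illness day at entry nor entry route, so the age effect can be distorted in a direction the protocol cannot fix

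*Protocol article*

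**What the plan says.** All places are in the protocol article; no separate analysis plan is at hand.

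- *Outcomes*: "The primary outcome is hospitalisation due to COVID-19". No time origin or window is attached.
- *Eligibility criteria*: the first route takes "COVID-19 patients aged 18 or older (as per definition patients with symptoms of an infection of any severity and positive test for SARS-CoV-2"), and they must be at home in isolation. The second takes "Patients aged 50 and older with a clinically urgent suspicion of COVID-19 (such as acute respiratory symptoms of any severity), without verification of SARS-CoV-2". All patients need at least one risk factor. Ages 18 to 49 have only the first route; from 50 both are open.
- *Intervention description*: "GP-ascertained begin of COVID-19 equals to day 1". The closing contact falls no later than three weeks after onset, so follow-up is not a fixed period from entry.
- *Plans for assessment and collection of outcomes*: the recorded items include the "date of assessment".
- *Statistical methods for primary and secondary outcomes*: the models cover "The potential effect of sociodemographic characteristics (age, gender, living situation), risk factors (as described above) on the severity of the disease" and on use of care services, allowing for clustering. The start of the disease is assigned to descriptive analysis. A hazard model is offered as an option for mortality only, without a stated time origin or delayed entry.
- *Methods for additional analyses*: adjustment refers back to the same regression models and adds no term.

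**The concern.** A patient taken in at home on day 2 of illness still has nearly all of the admission period ahead. One taken in on day 5 has already passed part of it without being admitted. If two groups differ in entry day, the earlier group shows more hospitalisations after entry even when the disease course is identical.

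Here the eligibility rule itself links the chance of early entry to age. Age is one of the effects to be estimated on the primary outcome, and the study's overall aim is to learn how risk factors affect disease course and use of care. There is no comparator, so model adjustment is the main protection for these estimates. The same rule also admits unverified cases only from age 50. Some of them will not have COVID-19 and so cannot be hospitalised because of it. That is a second age-linked influence, and it acts in the opposite direction.

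**Working it through.** The protocol states no sample size, power or event count, so there is no figure to reproduce. What follows is illustration.

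**Inputs from the protocol.** The suspicion route opens at age 50; day 1 is GP-set onset; closing is at three weeks (day 21) at the latest; the named model effects are age, gender, living situation and risk factors.

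**Assumptions not in the protocol.** Ten per cent of patients are ever admitted (p = 0.10). Time from onset to admission is gamma-distributed with shape 2.5 to 4 and median 6 to 9 days. There is no true age effect.

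**Step 1: observed days.** To day 21, entry on day 2 leaves 21 − 2 = 19 days and entry on day 5 leaves 21 − 5 = 16.

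**Step 2: remaining risk at entry on day d, given no admission so far.** With F the distribution function of onset-to-admission time, R(d) = p(1 − F(d)) / (1 − pF(d)). Over the grid, R(2) is 9.3–9.9%, R(5) is 6.3–8.6% and R(7) is 4.1–7.0%. The odds ratio is 1.17–1.53 for day 2 against day 5 and 1.46–2.54 for day 2 against day 7. These compare entry days, not age groups.

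**Step 3: convert to an age effect.** Let a share w of the 50+ group enter on day 2 and everyone else on day 5. The 50+ risk is wR(2) + (1 − w)R(5); the under-50 risk is R(5).

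- Upper end (shape 3, median 6, w = 0.5): F(2) = 0.0614 and F(5) = 0.3849. R(2) = 0.09386/0.99386 = 0.0944; R(5) = 0.06151/0.96151 = 0.0640. The 50+ risk is 0.0792. Odds ratio = (0.0792/0.9208) / (0.0640/0.9360) = 1.26.
- Lower end (shape 4, median 9, w = 0.1): F(2) = 0.0097 and F(5) = 0.1502. R(2) = 0.0991; R(5) = 0.0863. The 50+ risk is 0.0876. Odds ratio = 1.02.

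**Step 4: a second model, truncated at day 21.** Here the risk from entry day e is (F(21) − F(e)) / (1 − F(e)), with F a gamma (mean 7 or 9 days, SD 4) scaled to a 21-day risk of 5–20%. With entry on suspicion on day 2 or 3, entry on a test on day 4 to 6, and 30–100% of the 50+ group entering on suspicion, the apparent age odds ratio is 1.02–1.80. When entry days are equal it is 1.00 throughout.

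**Step 5: the opposing influence.** In the same model (21-day risk 10%, mean 7 days, day 3 against day 5), let a share q of suspected patients not have COVID-19. The 50+ risk becomes w(1 − q)R(3) + (1 − w)R(5), with R(3) = 0.0875 and R(5) = 0.0663.

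| q | w = 0.3 | w = 0.6 |
|---|---|---|
| 0 | 1.10 | 1.21 |
| 0.25 | 1.00 | 0.99 |
| 0.50 | 0.89 | 0.78 |

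The sign depends on q, which the protocol does not give.

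**The case against.** **The analysis plan may deal with this.** The methods section is permissive: it calls the analysis explorative and gives procedures as examples. An unseen plan could add timing terms. That stands as a caution, but the article is not silent. It names the modelled effects, refers adjustment back to them and leaves onset to description. An explorative label does not remove a systematic distortion.

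**Comorbidity effects.** A reader might infer that these are biased in the same way because GPs take in sicker patients sooner. No passage says so. Every participant has at least one risk factor and the entry rule does not differ by factor. What reaches the risk factors by rule is their correlation with age, and age is already in the model.

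**Confirmed patients.** A reader might also infer that the problem persists among patients who enter with a positive test. For them one rule applies from age 18, so the rule-based mechanism largely disappears. It survives only for patients aged 50+ who enter on suspicion and are confirmed later.

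**Under-50s need not be assessed later.** The positive test is a study criterion. The module itself is offered for confirmed and suspected patients with no stated age limit, and practices check study criteria among patients already in it. A younger suspected patient could therefore have an initial assessment before the test result. This stands, and it means the assessment date alone may be the wrong start of observation.

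**Adjustment has its own weakness.** Onset is a GP estimate, and patients who worsen quickly may make contact sooner, so entry day may partly reflect severity. This also stands and argues for reporting results both ways.

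**Conclusion.** The point holds for age. The entry rules permit different observed risk time on either side of 50, follow-up closes on an onset-anchored clock, and the named model terms do not account for it. The estimated age effect on hospitalisation can be distorted by illness day at entry and, possibly in the opposite direction, by suspected patients without COVID-19.

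Net direction and size cannot be fixed from the protocol. The age odds ratio of about 1.02–1.26 rests on assumed entry days of 2 and 5, 10–50% of the 50+ group entering early, 10% ever admitted, the assumed gamma times and no non-COVID suspects. Wider assumptions give up to 1.80; adding non-COVID suspects can bring it to 1 or below. The larger day-2-against-day-7 ratios should not be read as an age bias, because they suppose that whole groups enter on those days.

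**What to change.** In *Statistical methods for primary and secondary outcomes*:

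1. Add two covariates to the hospitalisation and other binary-outcome models: days from GP-set onset to the date the patient comes under observation (initial assessment, or the date the study criteria are met if later), and entry route (confirmed or suspected).
2. Report age effects with and without this adjustment, because entry day may partly reflect severity.
3. In any hazard model on the onset scale, let patients join the risk set on the day observation starts (delayed entry).
4. Tabulate entry day by age group and entry route.

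Cost: one or two more model terms and a few sentences of text. Onset date, assessment date and SARS-CoV-2 status are already collected; the date the criteria are met would have to be derivable from the module where it is later than the assessment. No additional patients are needed. The downside is that GP-set onset is measured with error, so adjustment will be imperfect.
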